## Assignment of interventions: allocation

### Sequence generation {16a} and concealment mechanism {16b}

After informed consent is given, participants will be randomized in the Web-CRF system (Norwegian University of Technology and Science) to one of three groups: (1) one 5-week period of working memory training, (2) two 5-week periods of working memory training, or (3) the active control group. The allocation sequence will be generated centrally within the Web-CRF system by a computer-generated randomization procedure, with randomization stratified by study center and restricted by permuted blocks of six to eight to maintain balance between groups within centers. Allocation concealment will be ensured by the Web-CRF system, and allocation is concealed and unavailable to the study team.

After randomization, group allocation is visible only to the Principal Investigator, the study secretary, and the coaches in the Web-CRF portal, who use this information to provide the participant with the correct login details, training materials and support during the training period.

### Implementation {16c}

A unique identifier is automatically generated within the digital Web-CRF system. Participant enrollment is conducted by the research nurse at each site. Following randomization, the Principal Investigator assigns training instructions to participants and communicates these to the coaches. Coaches have restricted access to the patient database and are only aware of the individuals they are currently coaching. No coaches are allowed to coach participants within their own geographic localization.

## Assignment of interventions: blinding

### Who will be blinded {17a}

All study personnel except for the Principal Investigator, coaches and the study secretary will be blinded for group allocation.

### Procedure for unblinding if needed {17b} and interim analyses {21b}

Treatment allocation will remain blinded throughout the trial and will not be disclosed before completion of the 48-month follow-up, except to the Principal Investigator, study secretary and coaches who require allocation information for trial administration and intervention delivery.

To facilitate planned analyses and publications during the study period, PhD candidates and senior researchers may be given access to de-identified datasets after completion of the baseline, 3-month, 6-month, 12-month, 24-month, and 48-month assessments, in which participants are assigned a unique mock study code. This identifier has no traceable link to the participant’s original study ID, and the allocation key will remain inaccessible to blinded study personnel. After all participants have completed the 48-month follow-up, full unblinding of treatment allocation will be performed.

## Data collection and management

### Plans for assessment and collection of outcomes {18a}

Data are collected at baseline and at 3, 6, 12, 24, and 48 months follow-up. The data management system Web-CRF will be used to input, manage and monitor data. Trained study nurses will gather background information, collect data from next-of-kin, and assess neuropsychiatric symptoms and activities of daily living. The EuroQOL 5D5L and BRIEF-A questionnaires will be sent to the participants and their next-of-kin for completion and then returned to the study secretary. The cognitive test battery and the Clinical Frailty Scale will be administered by researchers who are also experienced geriatricians or neuropsychologists. To ensure consistency, these researchers will receive training from a neuropsychologist prior to any testing. Saliva samples for genetic analysis will be collected by researchers and stored at room temperature, as required. Laboratory tests and MRIs are performed by the diagnostic laboratories at the sites. The cost-effectiveness analysis is described under Outcomes {12}.

### Plans to promote participant retention and complete follow-up {18b}

Detailed information about the study set-up and requirements will be sent to the participants before inclusion and the importance of completion will be stressed. Participants can stop the training or withdraw consent at any time without providing a reason to discontinue. In case of training cessation, the participants will be asked, but are not obliged, to complete the follow-up assessments. To promote retention, all participants will be coached during the training period, regardless of study group allocation. The research nurses remind patients of MRI and study-visit appointments, and we aim to coordinate the MRI examinations on the same day as the study visit.

### Data management {19} and plans for auditing trial conduct {23}

The data will be entered to the Web-CRF program on a secure server (Norwegian University of Technology and Science) by site staff. The Principal Investigator monitors and ensure that missing data are addressed as soon as possible. Datasets will be locked for further input after all participants have passed each milestone (3 months, 6 months, 12 months, 24 months, and 48 months). Informed consent, test material and questionnaires will be stored within a secure locker in a locked room. All MRI data acquired will be deidentified and saved in a study folder on a protected national research server.

### Confidentiality {27}

Study personnel and members of all boards are bound by the Norwegian health care confidentiality described in Health Personnel Act §5. Furthermore, no study results can be used or published without the approval of the Principal Investigator. Data is stored using a study identification code for each participant. Only the research team will have access to the key to the identification code list. This list will be documented and secured by the Principal Investigator in accordance with GCP after completion of the study. No identification details will be reported in publications.

## Statistical methods

### Statistical methods for primary and secondary outcomes {20a} and subgroup analyses {20b}

Baseline characteristics and other descriptive data will be summarized using appropriate descriptive statistics. Continuous variables will be described using the mean and standard deviation, or the median and interquartile range, as appropriate based on the distribution. Categorical variables will be described using counts and percentages. Simpler parametric or non-parametric comparisons may be used for descriptive or supplementary analyses.

The main analytical framework for longitudinal primary and secondary outcomes will be regression-based repeated-measures analyses, primarily using linear mixed-effects models (LMEs) (and generalized mixed-effects models for non-continuous outcomes, where relevant). These models account for within-participant correlation over time and allow inclusion of participants with incomplete follow-up data under standard model assumptions. Analyses of intervention effects will include time, treatment group, and the time × treatment group interaction as key terms. Relevant covariates (e.g., age, sex, and baseline values), as appropriate for the specific outcome, will be included in adjusted analyses. Given the heterogeneity of disease severity in MCI and risk of baseline imbalance in a moderate sample size, if systematic baseline differences are observed across the groups, a multidimensional composite covariate may be developed and included as an adjustment variable.

Planned contrasts will include comparisons of the single-training group and double-training group versus the active-control group at 6 months as the main outcome. If the double-training group is significantly better than the active-control group at 6 months, the estimated mean difference between the double-training and single-training groups will be tested at the 5% significance level to assess a possible dose–response effect. Pairwise contrasts between groups will also be estimated at 3 and 12 months to assess immediate and longer-term effects. Multiple comparisons will be applied using Holm–Bonferroni across the relevant tests. Results will include estimated marginal means with 95% confidence intervals, mean difference between groups with 95% CIs, and standardized effect sizes (Cohen’s *d* derived using the pooled baseline standard deviation).

The primary analysis will include all participants who completed randomization (modified intention-to-treat approach). Sensitivity analysis may be performed as per-protocol analyses, analyses with adherence included as a covariate, or as multiple imputation or tipping point analysis for missing data, as appropriate.

Repeated MRI-derived outcomes will primarily be analyzed using LMEs. Cortical thickness and gyrification analyses will be conducted using FreeSurfer’s specialized longitudinal linear mixed-effects module (vertex-wise analyses), with adjustment for relevant covariates. To account for multiple comparisons in mass-univariate MRI analyses, results will be corrected using false discovery rate (FDR) methods (planned threshold *q* < 0.05). Other repeated MRI-derived measures (e.g., diffusion, perfusion, and QSM measures, where applicable) will be analyzed using longitudinal mixed-effects models.

Moderator analyses will be conducted to investigate characteristics associated with differential responses to working memory training. These analyses will use LME models with interaction terms (e.g., moderator × time × treatment, as appropriate) to evaluate whether intervention effects differ across demographic and biological factors. In addition, an exploratory Elastic Net regression approach will be used to identify baseline variables associated with high response, particularly in the presence of multiple correlated candidate predictors. Variables identified in exploratory models will be examined further in post-selection regression analyses and interpreted as hypothesis-generating.

Statistical analyses will be performed in Stata (version 18), except for vertex-wise cortical MRI analyses, which will be performed in FreeSurfer using its longitudinal LME module.

The economic analysis of mild cognitive impairment in Norway will be conducted by merging data from national health registries with detailed patient and relatives’ questionnaires.

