## Outcomes {12}

### Primary outcome

The primary endpoint is the change in working memory function after 6 months measured by Spatial Span Backwards (from the Wechsler Memory Scale, third edition (WMS-III)) [39, 40].

To investigate immediate and long-term effects, the intervention groups will also be compared to the active control at 3, 12, 24, and 48 months. We will investigate a possible dose-dependent effect by comparing working memory performance, measured by spatial span backwards at 6, 12, 24, and 48 months, between the group receiving two periods of working memory training and the group receiving one period.

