### Sample size {14}

Sample size and power estimations are based on previously published data [43], assumed effect sizes (Cohen’s *d*) in the study population, and a comparison of two groups with equal sample sizes for simplicity. Stata 15 was used for the estimations, assuming an 80% power (beta = 0.8) and a 5% significance level (alpha = 0.05).

Work package 1: A comparable study reported a mean Spatial Span Backwards score of 5.80 (SD 2.00) at baseline in MCI [43]. A clinically significant effect between groups is defined as a mean difference of 0.5 times the standard deviation, resulting in a required sample size of 64 participants per group. With three groups, this totals 192 participants. Accounting for an anticipated 10% dropout rate, we plan to include a total of 213 (71 in each group).

Work package 2: Genetic variation and craniospinal clearance rate may independently influence or modify the effect of working memory training. The planned sample size is adequate to detect an effect comparable to the expected intervention effect, defined as a mean difference of 0.5 times the standard deviation. We should be able to assess possible effect modification within the intervention groups if it is strong (a Cohen’s *d* population parameter of about 1.0).

Work package 3: A comparable non-dementia study sample reported a mean RSS score of 6.6 (SD 8.8) [44]. Although no minimal clinically important difference has been established, we assume a similar mean difference between groups as estimated for the primary outcome in work package 1 (i.e. Spatial Span backwards score). Thus, the planned total sample size of 213 participants (71 in each group) is considered sufficient.

Work package 4: Assuming an annual dementia transition rate of 9.6% [3], a study population of 213 individuals is projected to yield 39 cases of dementia at the 24-month follow-up and 71 cases at the 48-month follow-up. However, these estimates are affected by uncertainties regarding the transition rate specific to working-memory-training populations and the applicability of international data to a Norwegian cohort.

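### The plan does not say that the 6-month primary contrasts come from a model conditioning on baseline Spatial Span Backwards, nor name centre, the stratification factor, in the analysis

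*Protocol article*

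**What the plan says.** Only the protocol article is at hand. Four places in it bear on this point.

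- **Design.** Sequence generation {16a} and concealment mechanism {16b} allocates participants "with randomization stratified by study center", using permuted blocks. The Introduction and the study-setting section give five clinics.
- **Endpoint.** The Primary outcome section states: "The primary endpoint is the change in working memory function after 6 months measured by Spatial Span Backwards".
- **Model.** Statistical methods {20a}/{20b} chooses linear mixed-effects models and fixes three key terms: time, treatment group and their interaction. On covariates it says: "Relevant covariates (e.g., age, sex, and baseline values), as appropriate for the specific outcome, will be included in adjusted analyses". The planned contrasts compare each training group with active control at 6 months, with Holm–Bonferroni across the relevant tests. Centre is not mentioned in this section or in the missing-data section {20c}.
- **Measurement.** Table 1 has Spatial Span Backwards taken at baseline and at every follow-up visit, so baseline could enter either as a covariate or as the first repeated measure. The text does not say which.

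**The concern.** The section describes a model but leaves open which version of it produces the primary result. Three readings fit the text:

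1. a between-group difference in the 6-month mean, with no use of baseline;
2. a between-group difference in change from baseline, which is what the time-by-group term estimates when baseline is in the outcome vector with free group means, and which matches the endpoint definition;
3. a 6-month difference conditional on baseline.

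These estimate the same treatment effect under randomisation, but with different precision. The third is at least as precise as the other two at any correlation. In addition, if baseline is already one of the repeated outcomes, adding baseline values as a covariate would use the same measurement twice.

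On centre, stratified allocation removes between-centre variation from the treatment comparison. A model without centre leaves that variation in the residual, so its standard errors are somewhat too large whenever centres differ.

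What is at stake is power for the primary contrasts and a single, pre-stated primary analysis. The validity of the randomised comparison is not in question.

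**Working it through.** **Inputs from Sample size {14}.** "A comparable study reported a mean Spatial Span Backwards score of 5.80 (SD 2.00) at baseline in MCI"; "A clinically significant effect between groups is defined as a mean difference of 0.5 times the standard deviation", that is 0.5 × 2.00 = 1.0 point, d = 0.5; alpha 0.05; power 80%; 10% dropout.

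**Inputs not in the document, so assumed.** Correlation r between baseline and 6-month scores: 0.3, 0.5, 0.7. Equal SD at both visits. Intraclass correlation (ICC) for centre: 0.05 as an illustration.

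**Step 1: the plan's own figure.** A two-sided two-sample t-test with d = 0.5, alpha 0.05 and 80% power needs 63.8, so 64 per group. This agrees with "resulting in a required sample size of 64 participants per group". Dropout: 192/0.9 = 213.3 and 64/0.9 = 71.1, against the stated 213 and 71. The stated figures reproduce. They use neither baseline nor centre.

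**Step 2: variance under each reading**, relative to the raw 6-month score:

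- raw score: 1
- change: 2(1 − r)
- conditional on baseline: 1 − r²

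The effective d is 0.5 divided by the square root of the factor.

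| r | Change: factor, d | Baseline-adjusted: factor, d | Variance, adjusted ÷ change = (1 + r)/2 |
|---|---|---|---|
| 0.3 | 1.40, 0.423 | 0.91, 0.524 | 0.65 |
| 0.5 | 1.00, 0.500 | 0.75, 0.577 | 0.75 |
| 0.7 | 0.60, 0.645 | 0.51, 0.700 | 0.85 |

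**Step 3: power with 64 per arm** (two-sample t-test at the effective d). The 0.025 level is the first Holm step if two contrasts share 5% (0.05/2).

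| r | Raw, 0.05 | Change, 0.05 | Adjusted, 0.05 | Raw, 0.025 | Change, 0.025 | Adjusted, 0.025 |
|---|---|---|---|---|---|---|
| 0.3 | 0.801 | 0.660 | 0.837 | 0.71 | 0.55 | 0.76 |
| 0.5 | 0.801 | 0.801 | 0.900 | 0.71 | 0.71 | 0.84 |
| 0.7 | 0.801 | 0.952 | 0.976 | 0.71 | 0.92 | 0.95 |

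At alpha 0.05, adjustment gains 0.837 − 0.801 = 0.036 to 0.976 − 0.801 = 0.175 over the raw score. Over change it gains 0.976 − 0.952 = 0.024 to 0.837 − 0.660 = 0.177. Below r = 0.5 the change contrast is worse than ignoring baseline.

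**Step 4: centre.** Including centre multiplies the variance by 1 − ICC. By normal approximation, power without baseline moves from 0.807 to 0.827 at ICC 0.05. With centre ignored, the actual two-sided alpha is 2[1 − Φ(1.96/√0.95)] = 0.044, slightly conservative. A simulation (4,000 runs, 64 per arm, five centres, r = 0.5, ICC 0.05) gave power 0.908 with baseline alone and 0.909 with baseline plus centre.

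**The case against.** The strongest reply is that a journal article condenses the plan, and that an exact covariate list, the handling of baseline and the form of the centre term are ordinary content for a statistical analysis plan that is not shown. The text names baseline values and says that relevant covariates will be included. Its list is illustrative, so centre is not excluded. If the adjusted model is primary, or if baseline is a repeated measure with a common mean across arms, there is essentially no loss. Much of this stands.

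A reader might infer that the primary model omits centre, or that the primary contrast is unadjusted and gives precision away. The document supports neither: centre is unnamed rather than ruled out, and no sentence makes an unadjusted contrast primary. A reader might also infer an inflated false-positive rate from leaving centre out. The direction is the opposite, and the effect is small.

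The 0.025 figures must not be read as the trial's power under Holm either, because the second contrast may be tested at 0.05. In a simulation with d = 0.5 in both training arms and no baseline adjustment, power under Holm was about 77% per contrast and 85% for at least one.

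What remains is that the section does set out a model and a covariate rule, and that rule allows primary analyses of materially different precision.

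**Conclusion.** The point holds in a limited form. Centre is the stratification factor and the analysis text does not name it. Baseline Spatial Span Backwards is not tied to the model that yields the 6-month primary contrasts. The text therefore permits a raw or a change contrast, each less efficient than conditioning on baseline.

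For assumed correlations from 0.3 to 0.7, the choice left open is worth about 4 to 17 points of power against the raw score and about 2 to 18 points against change, at alpha 0.05 with 64 per arm. These sizes rest on assumed correlations and an equal SD at both visits. They are the cost of an unadjusted choice, not a loss already built into the plan.

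Nearly all the gain comes from baseline. Centre belongs in the model so that the standard errors reflect the design. The stated sample size is not in error.

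**What to change.** In Statistical methods {20a}/{20b}, state that the 6-month primary contrasts come from one mixed model with fixed effects for centre, visit, group and group-by-visit, in which baseline Spatial Span Backwards is used once. Either of two forms will do:

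- baseline as a covariate, with only post-baseline visits as outcomes; or
- baseline as a repeated measure, with its mean constrained equal across arms.

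Use the same structure for the other repeated outcomes.

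The cost is a sentence or two of text and about four degrees of freedom for centre (five clinics minus one), merging very small centres if needed. No extra participants or assessments are required, and the sample-size calculation can stay as it is.

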### Trial design {8} and intervention description {11a}

#### Working memory training

This is a Norwegian multi-center, blinded three-arm, parallel-group randomized controlled trial (RCT) with block randomization and an allocation ratio of 1:1:1. The trial is designed within a superiority framework to evaluate whether adaptive working memory training improves outcomes compared with an active control condition, and to explore whether repeated training provides additional benefit (dose–response effect). The COGMED® program (Neural Assembly Int AB, Sweden) is a computerized adaptive program designed through repetitive tasks to improve working memory. One training period lasts about 5 weeks and consists of 40 min of daily adaptive training for 4–5 days a week, resulting in 20–25 training sessions. Individuals log on to a portal to train in the privacy of their homes, thus enabling logging of training time. The participants are randomized at study inclusion to one of three groups: (1) 5 weeks of adaptive working memory training (20–25 sessions), (2) 5 weeks of adaptive working memory training (20–25 sessions), repeated twice 1–2 months apart, or (3) 5 weeks (20–25 sessions) of Klondike solitaire on an online portal (active control group). These individuals self-report training frequency and times through a written log. All groups receive individual weekly coaching as per requisite from the COGMED® program. The use of an active control groups is based on the international consensus to improve quality of computerized cognitive intervention studies, as described by Simons et al. [33].

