#### Assessments

Baseline assessments are completed prior to randomization; thereafter, the participant will be followed at 3, 6, 12, 24, and 48 months (Fig. 1).

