### Secondary outcomes

#### Clinical outcomes

Secondary cognitive endpoints are scores on tests within the working memory domain at 3, 6, 12, 24, and 48 months post intervention assessments. Moreover, secondary endpoints are the RBANS composite score, scores on the executive function domain, scores on the Mini-Mental State Examination (MMSE), the Clinical Dementia Rating scale (total and sum of boxes), and conversion to dementia.

We consider the participants as having dementia when they fulfill the National Institute on Aging and Alzheimer’s Association (NIA-AA) 2011 criteria for all-cause dementia [41]:

Cognitive or behavioral symptoms that:Hinder the ability to function independently in activities of daily living or workConstitute decrease in functioning and performing from previous levelsCould not be explained by delirium or a major psychiatric disorderCognitive impairment detected through history taking and cognitive testingInvolves at least two of the following domains:Immediate learning and delayed memory (list learning, story memory, list recall, list recognition, story memory and figure recall index score from RBANS test battery)Reasoning, judgement and handling of complex tasks (Clinical Dementia Rating Scale, CDR).Visuospatial abilities (figure copy and line orientation index score from the RBANS test battery)Language (picture naming and semantic fluency index score from RBANS test battery)Behavioral and psychological symptoms (Neuropsychiatric Inventory Questionnaire (NPI-Q), and Mild Behavioral Impairment Checklist (MBI-C))

We require age- and education-adjusted scores at least 1.5 SD below the mean to consider a cognitive domain as affected. Affected behavior requires a minimum of one domain with the severity score 2 (moderate) or 3 (severe) or a NPI-Q sum score ≥ 3. To ensure consistency, dementia diagnoses will be discussed in consensus meetings involving experienced geriatricians and neuropsychologists.

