#### Quality of life and relatives stress (work package 3)

Participant and relative quality of life (QoL), as well as relative stress, will be measured at baseline and at 3, 6, 12, 24, and 48 months post-intervention.

The next-of-kin completes the Relative stress scale (RSS), a self-administered questionnaire assessing various aspects of proxy distress divided into the subscales “emotional distress,” “social distress,” and “negative emotions.”

QoL of participants and their next-of-kin will be assessed, with EQ-5D-5L, at baseline and at 3, 6, 12, 24, and 48 months post-intervention. Additionally, participants and their next-of-kin will complete the BRIEF-A at the aforementioned intervals. The BRIEF-A assesses executive function and self-regulation in daily life, covering two main indexes (metacognition and behavioral regulation), along with an overall summary score and three validity indicators. The BRIEF-A provides an indirect measure of QoL and relative stress, by assessing how executive function impacts daily life of the participants.

The combination of RSS, EQ-5D-5L, BRIEF-A, in addition to the Neuropsychiatric Inventory Questionnaire ensures solid information on QoL and relative stress.

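### On the baseline visit clock, the 3-month visit falls before or during the double group's second training period in nearly every permitted case, so 3-month contrasts with that group are not the immediate effect of two periods

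*Protocol article*

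**What the plan says.** All references are to the protocol article.

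- **Training schedule** (Trial design {8} and intervention description {11a}, Working memory training): "One training period lasts about 5 weeks and consists of 40 min of daily adaptive training for 4–5 days a week, resulting in 20–25 training" (the last figure counts sessions). The double group is assigned "2) 5 weeks of adaptive working memory training (20–25 sessions), repeated twice 1–2 months apart". The Abstract and the section on sequence generation make clear that this means two periods in all.
- **Visit clock** (Assessments): "Baseline assessments are completed prior to randomization; thereafter, the participant will be followed at 3, 6, 12, 24, and 48 months".
- **Competing clock wording**: Clinical outcomes says "Secondary cognitive endpoints are scores on tests within the working memory domain at 3, 6, 12, 24, and 48 months post intervention assessments", and the quality-of-life section says its measures "will be measured at baseline and at 3, 6, 12, 24, and 48 months post-intervention".
- **Contrasts at 3 months** (Primary outcome): "To investigate immediate and long-term effects, the intervention groups will also be compared to the active control at 3, 12, 24, and 48 months". The statistical methods section {20a} goes further: "Pairwise contrasts between groups will also be estimated at 3 and 12 months to assess immediate and longer-term effects". It then applies Holm–Bonferroni to the relevant tests, without listing them.
- **Dose comparison** (Primary outcome): the text sets out a comparison "measured by spatial span backwards at 6, 12, 24, and 48 months, between the group receiving two periods of working memory training and the group"; the group named last is the single-period one. Month 3 is not in that list. Section {20a} places the dose–response test at 6 months, conditional on double beating control there.

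**The concern.** The 3-month contrasts are meant to show immediate effects. That label needs the groups to have finished their assigned training, or at least to be at a known point in it. The single and control groups meet this: on a 5-week period they are all about 8 weeks past their last session. The double group does not. Depending on where each person's gap falls and how fast they train, some have had exactly the single group's course, and others are tested in the middle of a second course.

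Double versus control at 3 months would then estimate the first period plus an unfixed part of the second. Double versus single would compare either two identical completed courses or people at rest with people in training. Neither answers the question the label poses. If double versus single stays in the planned set, it may also take a place in the multiplicity correction without a clear estimand. What is at stake is the interpretation of secondary contrasts, not the primary analysis.

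**Working it through.** **Inputs.** Period length P is about 5 weeks. The plan's session count reproduces: 5 weeks × 4 days = 20 and 5 weeks × 5 days = 25. Read literally, the same figures allow P from 20/5 = 4 weeks to 25/4 = 6.25 weeks. The gap g is 1–2 months. One month = 365.25/12/7 = 4.35 weeks, so the 3-month visit is at week 13.0 and the 6-month visit at week 26.1.

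**Assumptions.** Visits are counted from baseline, training starts at baseline, and the gap runs from the end of period 1 to the start of period 2.

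**Formulas.** Period 2 starts at P + 4.35g and ends at 2P + 4.35g. The share completed at the visit is (13.04 − start)/P.

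| P (weeks) | g (months) | Period 2 (weeks) | 3-month visit |
|---|---|---|---|
| 5 | 1 | 9.3–14.3 | 74% through |
| 5 | 1.5 | 11.5–16.5 | 30% through |
| 5 | 2 | 13.7–18.7 | before it starts |
| 4 | 1 | 8.3–12.3 | after it ends |
| 4 | 1.5 | 10.5–14.5 | 63% through |
| 4 | 2 | 12.7–16.7 | 9% through |
| 6.25 | 1 | 10.6–16.8 | 39% through |
| 6.25 | 1.5 | 12.8–19.0 | 4% through |
| 6.25 | 2 | 14.9–21.2 | before it starts |

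**Thresholds for P = 5.** Finishing by month 3 would need g ≤ (13.04 − 10)/4.35 = 0.70 months, below the stated minimum of 1. Period 2 has not begun at the visit if g > (13.04 − 5)/4.35 = 1.85 months. In sessions, the 1-month gap gives (13.04 − 9.35) = 3.7 weeks × 4–5 per week, or about 15–18 of the second 20–25.

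**The exception.** With g = 1, finishing by month 3 needs 2P ≤ 13.04 − 4.35, so P ≤ about 4.35 weeks. With P = 4, the gap can be at most (13.04 − 8)/4.35 = 1.16 months.

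**Start lag.** The article states no interval between baseline and the first session. Any such lag moves period 2 later and strengthens the result.

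**Other clocks.**
- Counted from the end of period 1 (P = 5), the visit is at week 5 + 13.0 = 18.0. Period 2 ends between weeks 14.3 and 18.7, so it is over in most cases but not all.
- Counted from the end of all training, the visit always follows both periods.

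**Gap read as start to start.** With P = 5, a 1-month spacing (4.35 weeks) is shorter than the period itself and cannot be delivered. A 1.5-month spacing puts period 2 at weeks 6.5–11.5, before the visit. A 2-month spacing puts it at weeks 8.7–13.7, still running at the visit. Since part of the stated range is impossible on this reading, end to start is the coherent one.

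**Check at 6 months.** In the table, period 2 ends between weeks 12.3 and 21.2, which is 13.7 to 4.9 weeks before week 26.1. The primary visit follows both periods in every case.

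**The case against.** The other side has several good points.

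- **The clock is not settled.** Two sections describe the same visits as following the intervention. The Assessments wording is the more natural definition, but the point depends on it, so it has to be conditional.
- **A reader might infer that nobody in the double group has finished by month 3.** That is too strong. Fast trainers with 4-week periods and a gap near 1 month finish at week 12.3. The amount received also depends on training pace, not only on the gap.
- **A reader might infer that the plan would take a 3-month double-versus-single difference as early dose–response.** The documents do not support this. The Primary outcome section starts the dose comparison at 6 months, and section {20a} ties the dose–response test to 6 months. What remains is that the pairwise wording in {20a} makes no matching exception.
- **A reader might infer that the double group's mixed state dilutes single versus control, or that these contrasts are confirmatory.** Neither holds. The model has separate treatment groups, no pooling of the training arms is planned, and the 3-month contrasts are only said to be estimated in addition to the main 6-month outcome.
- **Double versus control at 3 months remains a valid randomised comparison** of assigned strategies at a fixed time, and it carries information on the first period. The fault is in its label.

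These points narrow the concern but do not remove it. On the clock the Assessments section gives, the label is wrong for the double group, and two current sections define different 3-month contrast sets.

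**Conclusion.** The point holds in a limited form. With visits counted from baseline and periods of about 5 weeks, the 3-month visit falls before or during the double group's second period across the whole 1–2 month gap, with 0% to about 74% of that period completed. Over the full 4 to 6.25 weeks that the session counts allow, the only exception is periods of about 4 weeks with a gap near 1 month.

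The 3-month contrasts involving the double group are therefore not the immediate effect of the two-period regimen. Including double versus single at 3 months conflicts with the Primary outcome section. The conclusion rests on the baseline clock and on a gap measured from end to start; it disappears if visits run from the end of all training. The 6-month primary contrast is not affected. This is an inexpensive correction that should be made, not a flaw in the main analysis.

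**What to change.** No change to training, schedule or visits is needed. In the Primary outcome section and section {20a}:

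1. Name single versus control as the 3-month immediate-effect contrast, and state that on a 5-week period it falls about 8 weeks after the last session.
2. Remove double versus single at 3 months from the planned pairwise contrasts, and so from the Holm–Bonferroni set, in line with the visits that the Primary outcome section lists.
3. Keep double versus control at 3 months as a randomised but interim comparison, labelled as made before the second period is complete.
4. Present any split of the double group by second-period sessions at the test date as descriptive only. Who has started depends on behaviour after randomisation, so the subsets are not comparable with the randomised single group.
5. Reconcile the visit clock in Assessments with the post-intervention wording in Clinical outcomes and the quality-of-life section. If the sponsor intends visits to run from the end of all training, saying so removes the need for items 1 to 4.

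The cost is a few sentences and one fewer 3-month contrast. Because the unblinding section allows coded datasets to be released after the 3-month assessments, the change should be made and dated before 3-month results are compared by group.
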